#### Experimental intervention

The rationale and development of the intervention has been described elsewhere [17]. In brief, the intervention is protocolised, with clear instructions on the selection, prescription and progression of exercise, behavioural elements and long-term physical activity promotion. The exercise intervention will be delivered in groups of around six to eight people, in suitable local venues such as leisure centres or gyms, led by a physiotherapist, and if needed an assistant. The physiotherapists and assistants will attend a one-and-a-half-day training programme which covers all elements of the intervention. Staff delivering the intervention will also be issued with a manual describing it in detail.

A pre-exercise assessment will estimate each participant’s fitness using a 6-minute walk test [18], and information on relevant co-morbidities and current exercise will be collected at this time. The classes will comprise aerobic exercise on static bicycles, and resistance exercises using dumbbells and weighted belts and jackets. The intensity of the aerobic exercise will be measured using the Borg scale of rating of perceived exertion (RPE) [19], modified for people with dementia [20]. The intensity of the exercise will increase, with the intention that by the final classes each participant should be working on the bicycle at low intensity (RPE = 2 [21]) for 5 minutes, and then at least at moderate (RPE = 4) intensity for 20 minutes, with part of this at hard (RPE = 6) intensity for those participants who are able; and in the resistance exercises performing ten repetitions with the ten repetition maximum weight, i.e. the heaviest weight that can be lifted ten times with good form. Each class will last approximately 1 hour, will be twice weekly with at least one free day between classes, and each participant will be scheduled to attend 29 classes over approximately 4 months.

The intervention group will be encouraged to begin some independent exercise whilst the exercise classes are still taking place, supported by the use of a local exercise opportunities booklet detailing local facilities and programmes, such as Exercise on Referral schemes and Walking for Health groups. These participants will also receive three phone calls and have one face-to-face meeting with the physiotherapist in the 8 months following the exercise classes, to support and encourage them to continue with independent exercise. Any participants who withdraw from the intervention, either during the exercise classes or the unsupervised exercise period, will be encouraged to remain in the study and complete the outcome measures at the 6-month and 12-month follow-up points.

Compliance with the intervention will be defined as participants who have attended 75 % of the scheduled exercise classes in the intervention arm.

### Intervention fidelity checks

A quality control (QC) visit will be made by the local intervention lead to the staff delivering the intervention in the first few weeks of their exercise classes. This is aimed principally at ensuring that the intervention is being delivered in a standardised manner, and that the physiotherapist and exercise assistant can demonstrate competency in all aspects of the intervention. The QC assessor will also provide clinical supervision and support to the intervention staff as needed.

Items assessed will include: correct adherence to the exercise procedures focusing on ensuring effective delivery of an adequate exercise dose; correct completion of all paperwork, especially the structured treatment forms which record the exercise intensity and duration (enabling accurate calculation of the exercise dose delivered); evidence of the use of a person-centred care approach with appropriate support given to participants; communication between the staff regarding participants’ progress and needs; and completion and return of adverse event documentation (where required). This visit will also provide support and advice to staff to enhance their clinical competencies and assist with smooth running of the exercise group. A second QC visit will be made after some of the formal behavioural support activities (such as goal setting) have been commenced. If possible, these activities will be observed, if this is not possible assessment will be via inspection of the documentation and discussion with the physiotherapist who carried out the activity, and corrective guidance will be given as needed. The QC assessor will also assess continued correct adherence to the exercise procedures, with an emphasis on the use of progressions and provision of adequate exercise challenges, and the correct completion of clinical records.

At the end of each of these visits feedback will be provided to the staff, and further visits arranged if problems are found in the QC assessment or if the staff need further support. A QC form will be completed and signed by both the assessor and the physiotherapist (provided that the latter agrees with its findings).

### Serious adverse event (SAE) and adverse event (AE) reporting

An adverse event (AE) is defined as any untoward medical occurrence in a participant which does not necessarily have a causal relationship with this treatment. These are most likely to be identified by the physiotherapist during the exercise sessions, from information at the sign-in, or after completion of the exercise sessions during support telephone calls or the face-to-face meeting.

As each participant will have had a pre-exercise assessment done, this will provide information on co-morbidities. The DAPA trial population is likely to include many participants over 70 years old and therefore common chronic diseases of older age will be anticipated, e.g. osteoarthritis. It is expected that participants will experience some uncomfortable effects of participation in the intervention, for example muscle or joint soreness in response to exercise. Provided these follow an expected pattern (e.g. as for delayed-onset muscle soreness), or need simple modifications to the exercise activity (e.g. changes to the bicycle seat height), or are non-serious exacerbations of existing medical conditions, they should not be considered as adverse events.

A serious adverse event (SAE) is an AE that fulfils one or more of the following criteria:Results in death;Is immediately life-threatening;Requires hospitalisation or prolongation of existing hospitalisation;Results in persistent or significant disability or incapacity;Requires medical intervention to prevent one of the above.

SAEs to be reported in DAPA have been defined as those that occur as the result of an incident during, or within 2 hours of completing the exercise sessions or follow-on physical activities. SAEs will be reported to the Trial Co-ordinating Centre within 24 hours of the physiotherapist becoming aware of them. The Trial Co-ordinating Centre is responsible for reporting adverse events to the sponsor and ethics committee within required timelines.

The relationship of SAEs to trial treatment will be assessed by the Chief Investigator and this will be recorded on the SAE form. All SAEs will be recorded in the trial database, and where appropriate, reported to and reviewed by the DMEC throughout the trial, and will be followed up to resolution.

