### Study oversight

The overall supervision of the trial will be carried out by the Trial Steering Committee (TSC). This committee comprises the Chief Investigator, trial manager, statistician, and four independent members (including the committee chair). The TSC will monitor trial progress and conduct, and provide expert advice. In addition, an independent Data Monitoring and Ethics committee (DMEC) comprising three independent members, will review the progress of the trial and review safety data as it emerges. The DMEC will consist of independent experts with relevant clinical research and statistical experience. During the period of recruitment into the trial, reports of the accumulating data will be supplied, in strict confidence, to the DMEC, along with any other reports that the committee may request. There is no formal interim analysis proposed.

All substantial amendments to the protocol will be submitted to the ethics committee for approval. All non-substantial amendments will be submitted to the ethics committee for notification purposes. In addition, all substantial and non-substantial amendments to the protocol will be notified on a regular basis to the Trial Steering Committee, Data Monitoring Committee and Trial Management Committee. Where appropriate, and of operational purpose, the amendments will be notified to the Principal Investigators and other relevant trial and clinical staff. Trial registers will be informed of substantial amendments.

The trial sponsor is the University of Warwick. The sponsor has no role in the trial design; collection, management, analysis or interpretation of data; writing of reports and submission for publication.

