We will use the Neuropsychiatric Inventory (NPI) [11]. This scale assesses 12 dimensions of possible behavioural disturbance in dementia, including important predictors of care breakdown like depression and agitation, using a screening strategy to save time. We will collect data using the Zarit Burden Inventory (ZBI) [12]. This short scale is the most commonly used dementia-specific carer burden tool. We will collect cost data using the Client Services Receipt Inventory (CSRI) [13]. This detailed questionnaire is used with a carer and covers all social, health care, medication use and out of pocket expenses. It will be adapted for DAPA.

For carers, we will record carer age, gender, ethnicity, and details about the relationship they have with the person with dementia and how much care they provide. They will be asked to complete the Zarit Burden Interview [12], which measures carer burden, and the EuroQol EQ-5D [10] measuring their own health-related quality of life. They will be asked to complete several measures regarding the person with dementia whom they care for: Bristol Activities of Daily Living (BADL) scale [8], Proxy QoL-AD [9], the number of falls and fractures the person has had, and the NPI [11].

Additionally, at the 6-month and 12-month follow-up interviews, the carer will be asked “How much benefit have you gained from being in the DAPA trial?” and “How much has the dementia of the person you care for changed in the past 6 months?” The CSRI is usually asked of the carer about the participant at this time point, but a person with no carer can give as much information as they are able.

These outcomes are all among those recommended by a consensus recommendation of outcome scales for non-drug interventional studies in dementia [14].

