We specified the sample size parameters as follows. We set the group difference of 2.45 ADAS-cog points. Initially, we set the pooled standard deviation at baseline at 6.3 ADAS-cog points based on a literature review [25]. We checked the value of the pooled standard deviation at baseline after 66 participants had been accrued into the trial, and revised this to 7.8 ADAS-cog points. There were no statistical or interim analyses undertaken and hence no inflation of the sample size for interim testing. We used 2:1 randomisation and made a small upward adjustment for this [26] (p.144 equation 3.2). This gives a sample size of 360 for alpha of 0.05 and a power of 80 %. Recognising that there might be clustering associated with the group format of the intervention, we inflated the sample using a design effect of 1.04 [intraclass correlation (ICC) = 0.01] in the intervention arm, assuming that there will be five participants per group (recognising that it may not be possible to achieve and retain eight recruits to each group), giving a sample size of 375. The sample size was further inflated to account for 20 % loss to follow-up, of which 10 % will be attributable to death. Thus a final sample size of 468 participants was set with 312 participants to be randomly allocated to the intervention arm and 156 participants to the control arm.

As the ADAS-cog takes up to 35 minutes longer to administer than the sMMSE, in order to reduce burden on the participants and contain the costs of the trial, we removed the Cornell Scale for Depression in Dementia (CSDD) from the protocol. The ISCTRN registration was updated with these amendments in December 2014.

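### Reportable SAEs are tied to exercise and to the physiotherapist, so SAE counts cannot be compared between the arms

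*Protocol article*

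**What the plan says.** All references are to the protocol article.

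- **Serious adverse event (SAE) and adverse event (AE) reporting.** An adverse event is defined broadly, with no causal link required, and seriousness follows the usual criteria (death, threat to life, hospitalisation and so on). Reportable SAEs are then restricted to "those that occur as the result of an incident during, or within 2 hours of completing the exercise sessions or follow-on physical activities". They go to the co-ordinating centre "within 24 hours of the physiotherapist becoming aware of them". Adverse events are "most likely to be identified by the physiotherapist during the exercise sessions, from information at the sign-in", or afterwards through the support calls and the face-to-face meeting. The Chief Investigator assesses the relationship to treatment.
- **Experimental intervention.** The classes, the pre-exercise assessment and the later physiotherapist contacts belong to the intervention arm: "These participants will also receive three phone calls and have one face-to-face meeting with the physiotherapist".
- **Randomisation/masking** and **Usual care.** Controls receive usual care. For physical activity they receive only the information sheet that both arms are given.
- **Choice of outcome measures** and **Table 1.** Carers are asked for "the number of falls and fractures the person has had, and the NPI". The Client Services Receipt Inventory (CSRI) covers health care use at baseline, 6 and 12 months. Neither is restricted to one arm.
- **Study oversight.** The DMEC "will review the progress of the trial and review safety data as it emerges".
- **Sample size.** Deaths are anticipated, in an allowance for "20 % loss to follow-up, of which 10 % will be attributable to death".

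**The concern.** The trial gives moderate- to hard-intensity exercise to a population expected to include many people over 70. A safety conclusion needs serious events to be found in the same way in both arms. Here both the definition of a reportable SAE and the person who starts the report depend on taking part in the exercise programme. An SAE table by arm would then reflect who was being watched as much as what happened. It could mislead in either direction: exercise may look harmful because only that arm can contribute events, or safe because the definition admits so few. The same limit applies to the SAE reports reaching the DMEC while recruitment continues.

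**Working it through.** The point rests on the definition and the route of ascertainment, and the plan gives no SAE rate to reproduce. The first three steps set the sections side by side. The fourth is an illustration on assumed rates.

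**1. Can a control participant generate a reportable SAE?** Two conditions must be met.
- *An incident in the window.* The window is attached to exercise sessions or follow-on activities. Controls have no sessions. Follow-on activity, as described under Experimental intervention, is the independent exercise that the physiotherapist supports in the intervention arm.
- *A reporter.* The only reporter named is the physiotherapist. The detection points named (sessions, sign-in, support calls, meeting) are all intervention contacts. The section also assumes that each participant has had a pre-exercise assessment, which is an intervention step.

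A generous reading might count a control's own activity after receiving the information sheet as follow-on activity. The first condition could then be met, but the second still could not by any route described. The expected control count is therefore essentially zero, independent of the true rate.

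**2. What is lost in the exercise arm?** The window applies to the incident, not to when the serious event appears. A complication arising days after an in-class fall is reportable. A serious event with no identified incident in the window is not.

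**3. Is the rule consistent with its own section?** The adverse event definition needs no causal link, and the Chief Investigator is to judge relatedness case by case. The reporting rule settles most of that judgement beforehand by timing and setting. An event outside the window never reaches the assessment.

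**4. Illustration of scale.** Inputs: 312 exercise and 156 control participants (Sample size). The true 12-month proportions p with a serious event are assumed. Losses and clustering are ignored.

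- Expected controls with an event = 156 × p.
- If both arms share p and are ascertained alike, the 95% CI half-width for the risk difference is 1.96 × √[p(1−p)(1/156 + 1/312)], where 1/156 + 1/312 = 0.009615.
- Power to detect a doubling (p in controls, 2p in exercise) is for a two-sided 5% test of two proportions, with pooled variance under the null.

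| Assumed p | Controls with an event | Reportable under the rule | CI half-width (percentage points) | Power for a doubling |
|---|---|---|---|---|
| 5% | 7.8 | about 0 | 4.2 | 45% |
| 10% | 15.6 | about 0 | 5.8 | 80% |
| 20% | 31.2 | about 0 | 7.7 | above 99% |

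For p = 10%: √(0.09 × 0.009615) = 0.0294, and 1.96 × 0.0294 = 0.058. A 1.5-fold increase would be detected with power of only 16%, 31% and 64%. Symmetric ascertainment would thus give useful but imprecise information on harm. The stated rule gives no between-arm information on SAEs at any of these rates.

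**The case against.** The strongest reply is that the trial does hold comparative harm data. Falls and fractures are asked of carers and the CSRI records health care use, in both arms, at visits made by masked assessors. Tying SAE reporting to exposure is an openly stated choice in a non-drug trial. It does not touch the primary ADAS-cog comparison, the sample size or the masking. Most of this stands, and it limits the point to SAEs.

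A reader might go further in four ways that the article does not support.

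- *That the trial cannot compare harm at all.* It can compare some harms, for the reason just given. The comparison is weak, though. Falls and fractures are absent from Table 1 and are listed only under carer report, carers are recruited only where available, and carers are not masked. Table 1 gives the CSRI's purpose as informing the health economics.
- *That these data will not be used for safety, or that the DMEC will see one arm only.* The article does not say so. It refers to a fuller protocol and to analysis plans still to be finalised, and the DMEC may ask for any other reports. All that can be said is that the article does not describe these data as safety outcomes.
- *That the rule covers only a tiny share of follow-up time.* Dividing class hours by the hours in a year leaves out follow-on activity, which the rule includes, and treats risk as evenly spread over the year.
- *That almost none of the anticipated deaths would be reportable.* The article gives no causes or timing of death, and its phrase on the share of losses due to death can be read in two ways.

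**Conclusion.** The concern holds for SAEs. The reporting rule and route make the control-arm count essentially zero by construction, so SAE counts cannot be compared between arms. In the exercise arm, serious events without an identified in-window incident are not reportable. The rule also conflicts with the section's own adverse event definition and weakens the DMEC's safety review. The conclusion about control counts rests on the text alone and assumes only that no control-arm reporting route exists beyond those described. The counts of about 8, 16 and 31 controls depend on the assumed rates and only show scale. Comparative data on some harms exist and the primary analysis is unaffected, so this is a should-fix matter and not a threat to the trial's main result.

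**What to change.** 1. Keep the 2-hour rule only as the trigger for 24-hour expedited reporting. State that SAE counts collected under it are not a between-arm comparison.
2. Name deaths, hospital admissions, falls and fractures over 12 months as safety outcomes.
3. Ascertain them identically in both arms at the existing masked 6- and 12-month visits, using the CSRI and the falls and fractures questions. Put these to the participant where there is no carer. Record deaths in both arms by the same procedure when a visit cannot take place.
4. Tabulate them by arm, with a risk difference and 95% CI, for the DMEC and the final report.
5. Reconcile the reporting rule with the adverse event definition in the same section.

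The cost is protocol wording, one extra table and a few questions for participants without a carer. Most of the data are already collected. Two limits remain: self-report of falls by people with dementia will be less reliable, and carers stay unmasked. The report should therefore show how many participants in each arm had a carer informant.

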### Data management and data checking

All data will be managed within the framework of the Data Protection Act 1998 and the standard operating procedures of WCTU. Data will be entered onto a bespoke application and will be stored on a secure WCTU server with daily, weekly and monthly back-ups.

All case report forms (CRFs) and accompanying papers (excluding consent forms) are stored in a lockable cabinet at WCTU in individual, numbered participant files. The files are kept in numerical order and have restricted access. Consent forms will be stored separately as they contain identifiable information; the file will be kept in a different cabinet to the CRFs. Intervention forms are anonymised and stored in a lockable cabinet. All data will be checked for completeness and validity prior to data entry. Field researchers will be requested to check data for completeness prior to returning the CRFs to the DAPA trial team at WCTU. A further check will be made by an appropriate member of the trial team and queries clarified by the completing researcher prior to data entry. Data will not be checked and entered by the same trial personnel.

A detailed Data Management Plan has been written which provides full details of the management of the data including the tracking and collection of data from sites and participants, and guidance is provided for telephone contact with participants and carers.

### Statistics

#### Sample size

At the time of applying for research funding, our sample size was based on the standardised Mini-Mental Status Score [5] as the primary outcome measure. ISRCTN registration was completed on 29 July 2011 at the same time as the original ethical submission specifying the sMMSE as the primary outcome. During the process of developing the protocol, and with feedback from the TSC and DMEC, we changed the primary outcome to the ADAS-cog. We submitted this substantial amendment to the protocol for ethical approval, and this was granted on 17 July 2012. This was well in advance of the first randomisation to the trial, which was undertaken on 1 February 2013. The reasons for the change were that the ADAS-cog is acknowledged to be more sensitive in detecting cognitive change in individuals with mild to moderate dementia than a variety of other measures, including the sMMSE [22]. The ADAS-cog is able to characterise different domains of cognitive performance better than the other measures and has been recommended by an expert task force as the cognitive outcome measure of choice for research using participants with moderate cognitive impairment [22]. Unlike many other tests of cognition, the ADAS-cog has an expert-agreed between-group mean difference of about 2 to 2.5 points [23, 24], although smaller differences can be worthwhile [7]. This means that we can use a valid but more sensitive primary outcome measure. The potential sample size efficiency using the ADAS-cog was substantial.

We specified the sample size parameters as follows. We set the group difference of 2.45 ADAS-cog points. Initially, we set the pooled standard deviation at baseline at 6.3 ADAS-cog points based on a literature review [25]. We checked the value of the pooled standard deviation at baseline after 66 participants had been accrued into the trial, and revised this to 7.8 ADAS-cog points. There were no statistical or interim analyses undertaken and hence no inflation of the sample size for interim testing. We used 2:1 randomisation and made a small upward adjustment for this [26] (p.144 equation 3.2). This gives a sample size of 360 for alpha of 0.05 and a power of 80 %. Recognising that there might be clustering associated with the group format of the intervention, we inflated the sample using a design effect of 1.04 [intraclass correlation (ICC) = 0.01] in the intervention arm, assuming that there will be five participants per group (recognising that it may not be possible to achieve and retain eight recruits to each group), giving a sample size of 375. The sample size was further inflated to account for 20 % loss to follow-up, of which 10 % will be attributable to death. Thus a final sample size of 468 participants was set with 312 participants to be randomly allocated to the intervention arm and 156 participants to the control arm.

As the ADAS-cog takes up to 35 minutes longer to administer than the sMMSE, in order to reduce burden on the participants and contain the costs of the trial, we removed the Cornell Scale for Depression in Dementia (CSDD) from the protocol. The ISCTRN registration was updated with these amendments in December 2014.

